# 1. PROTOCOL SUMMARY

## 1.1. Synopsis

Title: Electronic pillbox-enabled self-administered therapy versus standard directly observed therapy for tuberculosis medication adherence and treatment outcomes in Ethiopia: a multicenter randomized controlled trial (SELFTB trial)

Hypothesis: The use of a digital medication event reminder and monitor device-observed self-administered therapy provides non-inferior medication adherence and treatment outcomes for patients with TB compared with the standard in-person directly-observed therapy (DOT) in Ethiopia, one of the low-income countries with the highest burden of TB.

Objectives: Primary objectives:

1. To assess whether a digital medication event reminder monitor (MERM) device-observed self-administered therapy improves adherence in patients with TB compared with the standard DOT.
2. To assess whether MERM-observed self-administered therapy improves treatment outcomes in patients with TB compared with the standard DOT.

Secondary objectives:

3. To evaluate if MERM-observed therapy provides higher health-related quality-of-life (HRQoL) and lower catastrophic costs compared to the standard DOT
4. To evaluate the patient-reported usability and treatment satisfaction with MERM-observed self-administered TB therapy compared with the standard in-person DOT.

Outcome measures: Primary outcomes:

1. Level of adherence: Individual-level percentage adherence over the two-month intensive phase measured by adherence records compiled from MERM device vs. DOT records.
2. Sputum conversion: Participants with sputum smear converted following the standard two-month intensive phase treatment.

Secondary outcomes

3. Negative IsoScreen urine isoniazid test: Participants having at least one negative urine isoniazid test result (IsoScreen test, GFC Diagnostics Ltd, Bicester, England)

4. Adverse treatment outcome: Participants having at least one of the three events: treatment not completed; death; or loss to follow-up
5. Self-reported adherence: Participants who self-reported to have forgotten to take their medication
6. Health-related quality of life (HRQoL): The association between MERM-observed therapy and HRQoL, with the HRQoL measured and calculated for each participant by arm using the EuroQoL 5-dimension 5-level (EQ-5D-5L) score ranging from 0 to 1, with a higher score designating better HRQoL.
7. Catastrophic costs: Participants with overall TB treatment cost exceeding or equivalent to 20% of their income.

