### **5.2. Secondary objectives**

#### **5.2.1. HRQoL and catastrophic cost**

To evaluate if MERM-observed therapy provides higher HRQoL and lower catastrophic costs compared to the standard DOT

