#### **8.5.1.5. Sampling and sample size**

The sample size is calculated considering a 1-sided type I error of 2.5%, a power of 80%, 10% attrition rate, delta of 20%, non-inferiority margin, and a continuous outcome of percentage adherence over the two-month intensive phase, with a standard deviation of 36% and 79% of average adherence, assuming null hypothesis for both arms. The results yield a sample size of 57 in each arm for a total of 114 participants. We will do a  $\log_{10}$  transformation on the data, where a difference can be equivalently transformed into a ratio using a power ( $10^3$ ). The non-inferiority will be calculated as the log in the control minus the log in the intervention, which is equivalent to the log of the control divided by intervention.

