## **9. STATISTICAL ANALYSIS**

Descriptive summary measures will be used to report participant characteristics. Chi-square tests will be used to evaluate potential associations among categorical variables. To compare the level of adherence between study arms and among variables, independent t-tests will be done on log-

transformed adherence percentage of the expected 60 days. Effects of the arms and other adherence variables will be estimated using a geometric mean (GM) with geometric standard deviation (GSD) and mean ratios (MR) with 95% confidence intervals (CI). Log binomial regression will be conducted to identify risk factors of at least one negative isoniazid urine test and self-reported adherence of participants. Effects will be measured using adjusted relative risk (ARR) with 95%CI. A general linear model will be done on log-transformed adherence percentage to identify the effects of variables on participants' level of adherence. Effects will be measured using an adjusted mean ratio (AMR) with 95% CI.

Descriptive statistics including frequency and percentage will be used to describe the health state of the study participants. Multiple bar charts with cross-tabulation will be used to illustrate distributions of health states by study arms. Chi-square and Fisher's exact tests will be employed to compare the five EQ-5D-5L health domains by study arms. Kolmogorov–Smirnov, Shapiro–Wilk tests, and median values with interquartile range (IQR) will be used to summarize EQ-5D-5L index value/utility. Nonparametric Mann–Whitney U test will be employed to compare the difference in EQ-5D-5L index value/utility among study arms. A log-binomial model will be used to identify risk factors for lower HRQoL, which is having at least one health problem.

The overall TB treatment cost will be estimated by considering costs related to anti-TB drug pick-up, guardian costs, and coping costs over the two-month intensive phase. The proportion of study participants who faced catastrophic costs at a cut-off point of 20% will be estimated. A cross-tabulation will be employed to evaluate the distribution of catastrophic cost over the study arms and chi-square test will be used to test the association between catastrophic cost and study arms.

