To compare the TSQM scores between study arms, independent t-tests will be done on log-transformed scores. Effects of the arms will be estimated using a geometric mean (GM) with geometric standard deviation (GSD) and mean ratios (MR) with 95% confidence intervals (CI). A general linear regression will be done on log-transformed TSQM scores to identify the effects of variables on participants' level of satisfaction. Effects will be measured using an adjusted mean ratio (AMR) with 95% CI. In all analyses, a 5% significance threshold will be used to determine statistical significance.

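### Section 9 tests the five ordered EQ-5D-5L domains with chi-square and Fisher's exact tests, which ignore level order and cost power in these supporting comparisons

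*Protocol*

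**What the plan says.** The secondary objective in Section 5.2.1 is directional: "To evaluate if MERM-observed therapy provides higher HRQoL and lower catastrophic costs compared to the standard DOT". The Synopsis defines the HRQoL outcome on one scale, the "EuroQoL 5-dimension 5-level (EQ-5D-5L) score ranging from 0 to 1, with a higher score designating better HRQoL".

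Section 9 of the protocol treats the EQ-5D-5L in three ways:

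- Domains: "Chi-square and Fisher's exact tests will be employed to compare the five EQ-5D-5L health domains by study arms". Frequencies, percentages, cross-tabulations and bar charts by arm accompany these tests.
- Index value: "Nonparametric Mann–Whitney U test will be employed to compare the difference in EQ-5D-5L index value/utility among study arms".
- Risk factors: "A log-binomial model will be used to identify risk factors for lower HRQoL, which is having at least one health problem".

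The significance level is general: "In all analyses, a 5% significance threshold will be used to determine statistical significance". The protocol does not say whether the domain tests use all five levels or a collapsed version, and it names no effect measure for the domains.

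**The concern.** The answer to each EQ-5D-5L domain runs from no problems to the most severe category. A chi-square or Fisher's exact test on the arm-by-level table gives the same p-value however the levels are permuted. It spreads the comparison over up to four degrees of freedom and cannot separate a move towards fewer problems from any other difference in shape. A significant result says only that the two distributions differ.

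The domain comparisons are the planned between-arm tests that would show where quality of life changes, for example in usual activities or anxiety. The trial is small, so avoidable loss of power in each of them matters. The same paragraph already uses an order-respecting test for the index, so the nominal choice for the domains looks unintended. For adherence and treatment satisfaction, Section 9 promises mean ratios with 95% CIs; the domains get no equivalent.

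**Working it through.** **Step 1. Number of patients.** Section 8.5.1.5 gives the design inputs as "1-sided type I error of 2.5%, a power of 80%, 10% attrition rate, delta of 20%, non-inferiority margin", with a standard deviation of 36%. Then n per arm = 2 × (1.960 + 0.842)² × 36² / 20² = 50.9, rounded up to 51. With 10% attrition, 51 / 0.9 = 56.7, rounded up to 57. This agrees with the protocol: "The results yield a sample size of 57 in each arm for a total of 114 participants". The size was set for adherence, and no power is stated for HRQoL. The check therefore uses 51 and 57 per arm.

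**Step 2. Assumptions.** The protocol gives no domain distribution and no expected effect, so both are assumed. The control distributions (percent in levels 1 to 5, none to worst) run from 20% in every level to 85% with no problems. The effect is a proportional-odds shift: at each cut-point, odds of being at or better than that level in the MERM arm = OR × odds in the control arm. Example with control 40/30/20/8/2% and OR 2.5: the cumulative odds at the first cut are 0.40/0.60 × 2.5 = 1.667, so P(no problems) = 1.667/2.667 = 62.5%. The remaining MERM levels become 22.9, 10.4, 3.4 and 0.8%.

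**Step 3. Simulation.** At least 40,000 replicates per cell, two-sided 5%. Pearson chi-square on the non-empty levels, tie-corrected Mann–Whitney, and chi-square on none versus any problem. Power at 57 per arm:

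| Control levels (%) | OR | Chi-square, 5 levels | Mann–Whitney | None vs any |
|---|---|---|---|---|
| 40/30/20/8/2 | 1.5 | 11.6% | 21.5% | 18.6% |
| 40/30/20/8/2 | 2.5 | 49.8% | 72.4% | 67.2% |
| 55/25/12/6/2 | 2.5 | 41.1% | 64.9% | 63.8% |
| 25/35/25/10/5 | 2 | 31.2% | 52.6% | 41.3% |
| 70/17/8/4/1 | 3 | 40.1% | 64.3% | 64.7% |
| 20/20/20/20/20 | 2.5 | 56.1% | 77.7% | 59.5% |
| 85/10/3/1.5/0.5 | 2 | 8.9% | 20.8% | 20.8% |

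Over the whole grid at 51 and 57 per arm:

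- Five levels, OR 1.5: Mann–Whitney gains about 6 to 10 points.
- Five levels, OR 2 to 3: it gains about 12 to 25 points. The lowest single cell is 10.9, with 85% reporting no problems and 51 per arm.
- Five levels, OR 4 at 57 per arm: 7 to 25 points; the gain is smallest where both tests already have high power.
- None versus any, OR 1.5 to 3: 0 to 12 points when a quarter or more of control patients report no problems, and about 1 point or less once 60% do. The exception is the even spread of 20% per level, where the loss reaches about 18 points.

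**Step 4. Type I error.** With no shift, the rank test rejects in 4.8 to 5.2% of replicates and the five-level chi-square in 2.4 to 5.0%. The gain is not bought with false positives.

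**Step 5. Analytic check.** At equal noncentrality, a test with 80% power on 1 df (noncentrality 7.85) has 59.5% on 4 df, and one with 50% (3.84) has 30.8%. The simulated losses are of this order.

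**Step 6. A case against the rank test.** With control 40/30/20/8/2% and an assumed MERM profile of 55/8/20/13/4% (more patients with no problems and more with severe ones), 57 per arm, chi-square has 72% power and Mann–Whitney 8%.

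**The case against.** The strongest reply is that no stated objective or outcome is defined by domain. A reader might infer that the trial gives up power to show better HRQoL with MERM. The documents do not support that: the outcome is the 0-to-1 score, and its arm comparison already uses the Mann–Whitney test. This part of the reply stands in full and confines the point to the supporting domain comparisons.

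Second, the protocol never says that five levels are tested. Its risk-factor model uses a binary definition, and for a 2×2 table chi-square and Fisher's exact tests are ordinary choices. This stands in part. The binary definition belongs to a separate model and is not stated for the domain tests, while the cross-tabulated distributions beside those tests suggest five levels. A statistical analysis plan may settle the handling of levels, but the protocol itself fixes the choice of test.

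Third, the size of the loss depends on chosen distributions and shifts. That is so, and it is why only ranges are given.

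Fourth, a general-association test can detect changes that a rank test misses, as Step 6 shows. This is a real but small cost: the reversal needs a non-monotone change, which is not the directional question asked.

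Fifth, direction can be read from the planned tables and charts. It can, but informally and without an interval.

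A reader might also infer that the domain tests are invalid because of sparse cells. They are not: Fisher's exact test is named, and the simulated chi-square does not exceed 5% under the null.

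**Conclusion.** The point holds as one of efficiency and interpretation in a supporting secondary analysis, and its priority is minor. The named tests discard the order of the levels and report no direction or size. If five levels are tested, each domain comparison loses about 6 to 10 points of power at OR 1.5 and about 12 to 25 at OR 2 to 3; if the domains are dichotomised, mostly 0 to 12. These figures rest on assumed control distributions, a proportional-odds shift, 51 to 57 patients per arm and a two-sided 5% level; the protocol fixes only the sample size and the 5%. The index-value comparison is untouched, and no primary conclusion depends on this choice.

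**What to change.** In Section 9, replace the domain tests by a comparison of each EQ-5D-5L domain between arms on its five ordered levels. Use either the Mann–Whitney test already planned for the index or a proportional-odds model reporting an odds ratio with 95% CI per domain. The model is preferable if an effect size is wanted, because it supplies direction and precision. Keep the cross-tabulations and bar charts as description.

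The cost is one sentence of protocol text, with no new data or patients. The one statistical price is little power against a non-monotone change in profile, which the retained cross-tabulations would still show.

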#### **4. HYPOTHESIS**

- The use of a digital medication event reminder and monitor device-observed self-administered therapy provides a non-inferior medication adherence and treatment outcomes for patients with TB compared with the standard in-person DOT in Ethiopia, one of the low-income countries with the highest burden of TB

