## **5. OBJECTIVES**

### **5.1. Primary objectives**

#### **5.1.1. Treatment adherence**

To assess whether a digital medication event reminder monitor (MERM) device-observed self-administered therapy improves adherence in patients with TB compared with the standard DOT.

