#### **5.1.2. Treatment outcomes**

To assess whether MERM-observed self-administered therapy improves treatment outcomes in patients with TB compared with the standard DOT.

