### **6.1.2. Sputum conversion**

- Participant with sputum smear converted following the standard two-month intensive phase treatment.

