## 8.2. Trial design

The study will be a prospective, multicenter, randomized, controlled, non-inferiority, effectiveness-implementation hybrid type 2, two-arm trial. The study will not dictate diagnosis or treatment for TB; thus, it will not introduce or use new medications. Systematic and desk review methods will guide the study aimed at exploring the digital health ecosystem in Ethiopia.

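### Sputum conversion is a primary outcome of a non-inferiority trial but has no margin, assumed rate or power; the objectives ask for improvement, and Section 9 does not carry over the adherence margin

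*Protocol*

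**What the plan says.** **Hypothesis and design.** Protocol Section 4 says that the device-observed therapy "provides a non-inferior medication adherence and treatment outcomes for patients with TB". The synopsis says the same. Section 8.2 describes the design: "The study will be a prospective, multicenter, randomized, controlled, non-inferiority, effectiveness-implementation hybrid type 2, two-arm trial". Section 7 also speaks of non-inferiority for both adherence and treatment outcomes, and makes a non-inferior result the trigger for proposing scale-up to the Ministry of Health.

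**Objectives.** Section 5.1.1 asks whether "self-administered therapy improves adherence in patients with TB compared with the standard DOT". Section 5.1.2 reads "To assess whether MERM-observed self-administered therapy improves treatment outcomes in patients with TB compared with the standard DOT". Both are superiority questions.

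**Primary outcomes.** There are two: percentage adherence over the intensive phase (6.1.1) and sputum conversion (6.1.2), defined as "Participant with sputum smear converted following the standard two-month intensive phase treatment".

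**Sample size (8.5.1.5).** "The sample size is calculated considering a 1-sided type I error of 2.5%, a power of 80" per cent, with 10% attrition, a 20% non-inferiority margin, SD 36% and mean adherence 79% in both arms. This gives 57 per arm, 114 in total, and concerns adherence only. The section adds that non-inferiority will be calculated as log control minus log intervention.

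**Analysis (Section 9).** Adherence is compared by t-tests on log-transformed percentages, with mean ratios and 95% CIs. For categorical data, "Chi-square tests will be used to evaluate potential associations among categorical variables". The section closes with "In all analyses, a 5% significance threshold will be used to determine statistical significance". The words non-inferiority and margin do not occur. Analyses are named for the urine test, self-reported adherence, EQ-5D-5L, catastrophic cost and treatment satisfaction, but not for sputum conversion.

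**The concern.** A non-inferiority claim needs a margin and a rule that compares an interval with it. For sputum conversion the protocol has neither. Conversion is the only primary measure of treatment outcome, so half of the Section 4 hypothesis has no criterion by which it could be shown. A chi-square test of no association does not help. A significant result shows a difference, and a non-significant one puts no bound on how much worse the pillbox arm might be. A margin chosen after the data are seen would not be credible.

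For adherence the parts of a rule exist, but in different sections and not on one scale. The objectives add a third version of the question, superiority, which conflicts with the hypothesis and with the basis of the sample size.

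**Working it through.** **1. The plan's own figure.** Inputs from 8.5.1.5: margin 20, SD 36, true difference 0, one-sided alpha 2.5% (z = 1.960), power 80% (z = 0.842), attrition 10%.

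n per arm = 2 × (1.960 + 0.842)² × (36/20)² = 2 × 7.85 × 3.24 = 50.9, so 51 evaluable. 51/0.90 = 56.7, so 57. The stated 57 per arm reproduces, and it rests on adherence alone.

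**2. What 51 evaluable per arm gives for sputum conversion.** The protocol states neither a conversion rate nor a margin. Assumptions: equal true conversion p in both arms, from 80% to 95%; margins of 10 or 20 points; risk difference, normal approximation, one-sided 2.5%.

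SE = √(2p(1−p)/51). Power = Φ(margin/SE − 1.960). Smallest margin with 80% power = 2.80 × SE.

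| Assumed conversion | SE (points) | Power, 10-point margin | Power, 20-point margin | Smallest margin with 80% power | n per arm for 80% power at 10 points (after 10% attrition) |
|---|---|---|---|---|---|
| 95% | 4.3 | 64% | over 99% | 12 points | 75 (84) |
| 90% | 5.9 | 39% | 92% | 17 points | 142 (158) |
| 85% | 7.1 | 29% | 81% | 20 points | 201 (224) |
| 80% | 7.9 | 24% | 71% | 22 points | 252 (280) |

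Worked line, p = 90%: SE = √(2 × 0.90 × 0.10/51) = 0.0594. Power at 10 points = Φ(0.10/0.0594 − 1.960) = Φ(−0.28) = 39%. Smallest margin = 2.80 × 0.0594 = 0.166.

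**3. The adherence margin on the scale analysed.** Sections 8.5.1.5 and 9 work with a log difference, which is a ratio. Section 8.5.1.5 does not say whether the 20% is absolute or relative.

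- 20 points below 79%: 79/(79 − 20) = 79/59 = 1.34 as control/intervention.
- 20% relative loss: 1/0.80 = 1.25, which is 0.80 × 79 = 63.2%, or 15.8 points below 79%.

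The sample size depends only on SD/margin = 36/20, so its reproduction does not settle which reading is meant. Both conversions take 79% as the reference, whereas Section 9 compares geometric means.

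**4. The 5% threshold.** Section 9 does not state whether it is one-sided or two-sided. Read as two-sided, it corresponds to a 95% CI, whose relevant limit has a one-sided error of 2.5%, as in 8.5.1.5. Read as one-sided, it would double that error.

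**The case against.** **The statistical analysis plan may hold the method.** It is not at hand, and the choice of test for conversion could properly be left to it. That stands for the test. It does not cover the margin and the power, which the protocol itself states for one primary outcome and omits for the other while claiming non-inferiority for both.

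**The adherence rule is nearly complete.** A reader might infer that Section 9 tests the wrong null hypothesis for adherence. The documents do not support that. Section 8.5.1.5 fixes a margin, a one-sided 2.5% error and a log contrast, and Section 9 reports the mean ratio with a 95% CI on the same log scale. What is missing is the sentence that compares them, and a margin in the same units.

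**The error rates need not conflict.** A reader might infer a clash between 5% and one-sided 2.5%. On the usual two-sided reading there is none; only the sidedness is unstated.

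**Nothing says that non-significance will count as non-inferiority.** A reader might infer this from the chi-square test and the 5% threshold. No section states such a rule, so an inflated false-positive rate cannot be attributed to the plan. The point is only that the named test cannot support the claim.

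**The objectives may be loose drafting.** The hypothesis, design and Section 7 agree on non-inferiority. This is fair: the wording alone would be a minor correction. It still needs correcting, because the objectives state what the trial sets out to show.

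**Conclusion.** Wrong as written. The firm part is sputum conversion: followed as it stands, the protocol cannot support its non-inferiority claim on treatment outcome, because no margin, assumed rate or power exists and the only applicable test addresses a different question. The lack of a margin depends on no assumption. The size of the power problem does: it uses assumed conversion of 80% to 95%, equal true rates, a normal approximation and 51 evaluable per arm. Under these assumptions a 10-point margin is underpowered throughout, and 80% power requires a margin of about 12 to 22 points. Whether a margin that wide is defensible is for the investigators to justify.

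The adherence part is narrower: a rule in 8.5.1.5 that Section 9 does not carry over, and a margin that could mean a ratio of 1.34 or 1.25. The objectives contradict the hypothesis and must be aligned with it.

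**What to change.** 1. **Objectives.** Reword 5.1.1 and 5.1.2, and the matching synopsis lines, to ask whether the pillbox strategy is non-inferior to DOT, with superiority tested only after non-inferiority is shown.
2. **Adherence.** State the 8.5.1.5 margin as a control/intervention ratio and say which reading of 20% it represents. In Section 9, conclude non-inferiority if the upper limit of the two-sided 95% CI of that mean ratio lies below the margin. Say that the 5% threshold is two-sided, so that it equals one-sided 2.5% for this purpose. Keep the rule on the ratio scale; a rule in raw percentage points would conflict with the log-scale analysis.
3. **Sputum conversion.** Either (a) write a justified margin and an assumed conversion rate into 8.5.1.5 with the power available at 51 evaluable per arm, and in Section 9 compare the 95% CI of the risk difference with that margin; or (b) make conversion a secondary outcome reported as an estimate with its CI, and limit the non-inferiority claim in Section 4, the synopsis and Section 7 to adherence.

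The cost is protocol wording and one design decision, to be taken before outcome data are seen. Neither option needs extra patients, provided that under (a) the power at the present size is stated and accepted. Insisting on 80% power at a 10-point margin would need more (for example 158 per arm at an assumed 90% conversion). The price of (b) is a narrower claim on treatment outcome.
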